# Protocol for a prospective, cluster randomized trial to evaluate routine and deferred dialysis initiation (RADDI) in Chinese population

**DOI:** 10.1186/s12882-019-1627-0

**Published:** 2019-12-09

## Abstract

**Background:**

The timing of when to initiate dialysis for progressive chronic kidney disease (CKD) patients has not been well established. There has been a strong trend for early dialysis initiation for these patients over the past decades. However, the perceived survival advantage of early dialysis has been questioned by a series of recent observational studies. The only randomized controlled trial (RCT) research on this issue found the all-cause mortality, comorbidities, and quality of life showed no difference between early and late dialysis starters. To better understand optimal timing for dialysis initiation, our research will evaluate the efficacy and safety of deferred dialysis initiation in a large Chinese population.

**Methods:**

The trial adopts a multicenter, cluster randomized, single-blind (outcomes assessor), and endpoint-driven design. Eligible participants are 18–80 years old, in stable CKD stages 4–5 (eGFR > 7 ml/min /1.73 m^2^), and with good heart function (NYHA grade I or II). Participants will be randomized into a routine or deferred dialysis group. The reference eGFR at initiating dialysis for asymptomatic patients is 7 ml/min /1.73 m^2^ (routine dialysis group) and 5 ml/min/1.73 m^2^ or less (deferred dialysis group) in each group. The primary endpoint will be the difference of all-cause mortality and acute nonfatal cerebro-cardiovascular events between the two groups. The secondary outcomes include hospitalization rate and other safety indices. The primary and secondary outcomes will be analyzed by appropriate statistical methods.

**Discussion:**

This study protocol represents a large, cluster randomized study evaluating deferred and routine dialysis intervention for an advanced CKD population. The reference eGFR to initiate dialysis for both treatment groups is targeted at less than 7 ml/min/1.73m^2^. With this design, we aim to eliminate lead-time and survivor bias and avoid selection bias and confounding factors. We acknowledge that the study has limitations. Even so, given the low-targeted eGFR values of both arms, this study still has potential economic, health, and scientific implications. This research is unique in that such a low targeted eGFR value has never been studied in a clinical trial.

**Trial registration:**

The trial has been approved by ClinicalTrials.gov (Trial registration ID NCT02423655). The date of registration was April 22, 2015.

## Background

Over the past two decades, the number of uremic patients that has received renal replacement therapy (RRT) has increased worldwide [1]. According to a rough estimate, the number of dialysis patients in China in 1999 was 42,000 cases and increased rapidly to 608,000 cases in 2015 [2]. The annual cost of dialysis treatment alone reached 429 million RMB in 2015 [2]. The rapid increase of dialysis patients has brought a heavy economic burden on Chinese society.

The strong trend of early dialysis initiation for end-stage kidney disease (ESKD) patients over recent decades makes the burden even greater. Data from the United States showed that the proportion of new dialysis patients with glomerular filtration rate (GFR) ≥10 ml/min/1.73m^2^ increased rapidly from about 10% in 1996 to around 50% in 2008 [3]. Between years 2000–2004 and 2005–2009, mean estimated GFR (eGFR) at dialysis initiation increased from 9.8 to 11.0 ml/min/1.73 m^2^ [4]. Early dialysis initiation not only increases the cost of medical treatment but also has no additional benefit for patients in long-term outcomes. Observational data showed that the short-term or long-term survival was not affected for chronic kidney disease (CKD) patients with stable low GFR (≤5 ml/min/1.73m^2^, and even ≤2 ml/min/1.73m^2^) before dialysis treatment [5, 6]. A recent retrospective cohort study found no statistically significant survival difference for early compared with later dialysis initiation (interpolated eGFR at dialysis therapy initiation ≥10 ml/min/1.73m^2^ vs. < 10 ml/min/1.73m^2^) [7]. Furthermore, some data even showed that early initiation seemed to produce an additional burden to patients and the health care system [5, 6, 8]. The Initiating Dialysis Early and Late (IDEAL) study, the only RCT research on this issue, found that the all-cause mortality, comorbidities, and quality of life showed no difference between early (GFR 10–14 ml/min/1.73m^2^) and late (GFR 5–7 ml/min/1.73m^2^) dialysis starters [9]. However, this study is limited by the condition that the difference for average GFR between two groups (12 ml/min/1.73 m^2^ vs. 9.8 ml/min/1.73m^2^) was not great. Moreover, the achieved GFR were relatively high for both groups. Thus, several major renal organizations have reassessed the risks and benefits of the practice of initiating early RRT [10–14]. The Canadian Society of Nephrology released a clinical practice guideline in which an “intent-to-defer” approach for dialysis initiation and strategy to initiate dialysis in the absence of symptoms in patients with an eGFR of 6 ml/min /1.73 m^2^ or less was recommended [12]. In this guideline, the specialists also expressed that the optimal management of patients with an estimated GFR of 6 ml/min per 1.73 m^2^ or less was based on limited data. The updated KDOQI (Kidney Disease Outcomes Quality Initiative) guideline emphasized that the decision to initiate maintenance dialysis “should be based primarily upon an assessment of signs and/or symptoms … rather than on a specific level of kidney function in the absence of such signs and symptoms.” [14]

The timing for initiating dialysis for ESKD patients is an important issue yet has not been well established, therefore, we have designed the study “Routine and Deferred Dialysis Initiation (RADDI)” to evaluate the efficacy and safety of deferred dialysis initiation.

## Methods

### Study design

The RADDI trial (the newest protocol version was 4.0, OUPM2017-12-25 on 25 Dec 2017) is a parallel assignment, prospective, single-blind (outcomes assessor), multicenter trial involving 16 clinical centers in China (see Fig. 1. Diagram of the study design).

**Fig. 1 Fig1:**
[figure not shown]
Diagram of the study design

### Main inclusion criteria

Participants aged 18–80 years oldNondialysis-dependent stable CKD stage 4–5 patients (eGFR > 7 ml/min /1.73 m^2^)Heart function: grade I or II (NYHA Functional Classification)

### Main exclusion criteria

Subjects who meet one of the following conditions shall not be included in the trial:
Patients with estimated short life expectancy (due to causes other than kidney disease);Acute infection occurred within the past month;Myocardial infarction, stroke events, or being diagnosed with heart function of NYHA class IV within the past 3 months;Uncontrolled malignancy;Active viral hepatitis;Active rheumatic disease;Pregnant women, women intending to conceive after enrollment or breastfeeding women;Patients scheduled to have transplantation during the study period;With indices requiring emergency dialysis;eGFR less than 7 ml/min/1.73m^2^ in first visit;Participating in other clinical studies that could impact this study;Unable to provide written informed consent.

### Trial intervention and visit schedule

#### Randomization

Cluster randomization was utilized. The intervention was applied at the facility level to avoid the possibility of experimental contamination at the patient level. Sixteen tertiary hospitals across China have been randomly assigned to the routine and deferred dialysis groups using a random number generator. At each site, on referral to the study, participants will be sequentially allocated a unique identifying number to be used for all subsequent study documentation. This will ensure confidentiality is maintained.

#### Blinding

Assessors for the primary outcome in the study will be blinded for the duration of the trial. Assessors for the secondary outcomes will not be blinded.

#### Pre-inclusion visit

Eligible patients will be asked to give their informed consent. The CKD-EPI (Chronic Kidney Disease Epidemiology Collaboration) formula is used to estimate GFR for participants (based on serum creatinine, as shown in Table 1). The pre-inclusion visit allows each putative inclusion to be validated via selection and validation procedures by the responsible researchers. Once approved by the selection and validation procedures, patients will undergo the inclusion visit.

**Table 1 Tab1:** CKD-EPI formula used to estimate GFR

Gender	serum creatinine (Scr)	CKD-EPI formula
female	≤0.7 mg/dL	eGFR = 144 × (Scr/0.7)^-0.329^X(0.993)^age^
	Scr > 0.7 mg/dL	eGFR = 144 × (Scr/0.7)^-1.209^X(0.993)^age^
male	Scr ≤0.9 mg/dL	eGFR = 141 × (Scr /0.9)^-0.411^X(0.993)^age^
	Scr > 0.9 mg/dL	eGFR = 141 × (Scr /0.9)^-1.209^X(0.993)^age^

### Inclusion visit

During the inclusion visit, baseline laboratory tests will be obtained for patients eligible for this trial.

### Intervention

#### Routine dialysis initiation group

In this control group, the decision whether or not to initiate dialysis in progressive CKD patients will be made based on a flow paradigm of clinical indicators (Fig. 2). Researchers will start dialysis treatment when a patient’s eGFR reaches 7 ml/min/1.73m^2^ in asymptomatic patients. Alternatively, researchers will initiate dialysis when patients have clinical indications listed below:
Patient’s modified Kraemer index is > 6 [15] (Table 2) or with overt fluid overload after trying all conservative means (including appropriate medicines);Patients with subjective global assessment (SGA) assessment grade C;Patients with indications for emergency dialysis (Table 3);Patients with severe symptoms, which cannot be relieved by conservative treatment.

**Fig. 2 Fig2:**
[figure not shown]
The flow paradigm of clinical indicators for dialysis initiation

**Table 2 Tab2:** The modified Kraemer index to evaluate symptoms of hypervolemia

Clinical score of symptoms of hypervolemia	
Systolic Blood pressure ≥ 180 (new onset)	+ 2
Pretibial edema, weak	+ 2
Chronic coughing (new)	+ 2
Dyspnoea at rest, recumbent	+ 2
Pretibial edema, severe	+ 3
Dyspnoea at rest, one cushion	+ 3
Dyspnoea at rest, two cushions	+ 4
Dyspnoea at rest, sitting	+ 6

**Table 3 Tab3:** Indications for emergency dialysis

Patients meet any of the following conditions may begin emergency dialysis after adequate drug therapy:	
(1)oliguria or anuria for more than 2 days	
(2)hyperkalemia: blood potassium > 6.5 mmol/L	
(3)carbon dioxide combining power (CO_2_CP) < 13 mmol /L	
(4)acute pulmonary edema	
(5)Gallop rhythm of the heart	

#### Deferred Dialysis initiation group

In this intervention group, similar flow paradigm of clinical indicators (Fig. 2) for initiating dialysis are used. Researchers will not start dialysis treatment for patients who are asymptomatic until their eGFR is below 5 ml/min/1.73m^2^. If safe for patients, investigators will postpone dialysis as late as GFR 2 ml/min/1.7m^2^. Clinical indications for initiating dialysis are the same as listed above for the routine dialysis initiation group.

### Follow-up

All patients will attend a study visit every 3 months before and after dialysis is performed.

For each visit, a clinical and biological evaluation will be performed (Table 4). Special tests such as body composition (not mandatory, only for sites having the device), ultrasound cardiography (UCG), chest X-ray, kidney ultrasound will be taken annually. The well-validated short form health survey questionnaire 36(SF-36) survey instrument will assess health-related quality of life. Nutritional status of patients is evaluated using the SGA scale, which includes medical history and a physical examination. Medical history consists of 5 categories: (1) history of weight loss, (2) dietary intake change, (3) gastrointestinal symptoms, (4) functional capacity, and (5) metabolic demand related to the underlying disease. Physical examination focuses in the detection of muscle wasting, loss of subcutaneous fat, and the presence of edema. Based on this information, according to the subjective evaluation of the observer, the nutritional diagnosis is defined and the patients are classified as: (A) well-nourished, (B) moderately (or suspected of being) malnourished, or (C) severely malnourished. Serious adverse events, acute nonfatal cerebro-cardiovascular events, and hyperkalemia will be reported prospectively. Moreover, the cost for patient spending on CKD disease will be recorded.

**Table 4 Tab4:** Schedule for visits

Parameters recorded	Pre-inclusion visit	inclusion visit	Before dialysis		Initiation dialysis	After dialysis	
			Quarterly visit	every 6 months visit		Quarterly visit	every 6 months visit
Medical history	X						
Symptoms	X	X	X		X	X	
Physical evaluation	X	X	X		X	X	
SGA		X		X	X		X
QOL		X		X	X		X
CBC		X	X		X	X	
Alb		X	X		X	X	
Scr	X	X	X		X	X	
eGFR	X	X	X		X	X	
SI and Ferritin		X		X	X	X	
iPTH		X		X	X	X	
BNP		X		X	X		X
CRP		X		X	X		X
DW					X	X	
UF					X	X	
UO					X	X	
Clinical events			X		X	X	
Costs			X		X	X	

*SGA* subjective global assessment, *QOL* quality of life (by short form 36), *CBC* complete blood count, *Alb* Albumin, *Scr* serum creatinine, *eGFR* estimated glomerular filtration rate, *SI* serum iron, *iPTH* Intact parathyroid hormone, *BNP* brain natriuretic peptide, *CRP* C reactive protein, *DW* dry weight, *UF* ultrafiltration amount, *UO* urine output. Physical evaluation includes vital signs (blood pressure, heart rate, body weight, height, etc.), degree of edema and other positive signs

### Endpoints

#### Primary endpoint

The primary endpoint will be all-cause mortality and acute nonfatal cerebro-cardiovascular events before and after dialysis initiation. We will compare proportions of all-cause death rates and acute nonfatal cerebro-cardiovascular events before and after dialysis treatment between two groups.

#### Secondary endpoints

The secondary outcomes will allow the investigators to:
Assess the hospitalization rates by comparing proportion of patients who are admitted to hospital before and after dialysis treatment between the two groups;Assess the nutritional status before and after dialysis treatment between the two groups by using SGA assessment and serum albumin levels;Assess patient reported quality of life by using SF-36.Assess the complications of dialysis after dialysis treatment between the two groups;Implement a cost study.•Assess arteriovenous fistulas rate and catheter usage as blood access at first dialysis.

### Economic evaluation

#### Cost measurement

To assess the total cost of each group, the number of resources consumed will be prospectively collected for each patient (drugs, medical devices, consultations, hospitalization, etc.). The receipts from each visit will be used to record the patient’s costs during the follow-up period.

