### Statistical analysis

#### Sample size

In this study, a cluster randomized design is used. The primary endpoint of the study is death rate, which will be determined by survival analysis. According to the IDEAL study, the death rate was 37% during a median follow-up period of 3.59 years [9]. Because we include relatively stable patients the mortality rate may be lower; we assume the death rate will be 30% or less within 3 years. The project selection window for patient enrollment is 30 months. Sood et al. found an adjusted facility-level intraclass correlation coefficient (ICC) of 0.031 in their work [16]. We get 8 clusters per group. Scholars have proposed that a sample size calculated assuming individual randomization can be inflated by a Design Effect (DE) to reach the required level of statistical power under cluster randomization [17]: DE = 1+ (m-1) ρ, where m is the number of individuals per cluster and ρ is the ICC.

If we assume that alpha = 5%, (1-beta) = 80%, patients are assigned 1:1, a difference of 10% in death rates between these two groups is considered acceptable. We use log-rank tests to get the events (87 vs 57) with the Power Analysis and Sample Size Software, version 13 (NCSS, LLC. Kaysville, Utah, USA) and the number of individuals per group is 473. Thus, the number of total events under the consideration of cluster effects is 198 (128 vs 70). This is an endpoint driven study. We will complete the study when we get enough endpoint events, which is 198 events.

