#### Analysis

In this randomized controlled trial, equivalence tests for two proportions in a cluster-randomized design will be performed according to requirements in the CONSORT (Consolidated Standards of Reporting Trials) statement. Sociodemographic, clinical, and economic data will be analyzed per group.

Baseline characteristics at enrollment will be reported as the mean and standard deviation (SD) for continuous variables and percentage for categorical variables. Continuous variables not normally distributed will also be presented as a median and interquartile range.

Missing data will be imputed using multiple imputation regression methods.

Cox analysis will be used to compare all-cause mortality, acute nonfatal cerebro-cardiovascular events, and hospitalization before and after dialysis treatment between the two groups.

T-tests will be performed to compare nutritional status, quality of life, residual renal function (urine volume), and medical expenses based on a data-paired analysis (before-after study). Continuous data will be compared using a paired t-test if the variable is normally distributed or Wilcoxon test for non-parametric variables. The MacNemar test will be used for categorical variables (Fleiss test, if necessary).

Statistical significance will be considered at a value of *p* ≤ 0.05. All statistical analyses will be performed with SAS, version 9.4 (SAS Institute, Cary, NC; USA).

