Recently, the Canadian Kidney Knowledge Translation and Generation Network published its study protocol “Knowledge Translation Interventions to Improve the Timing of Dialysis Initiation: Protocol for a Cluster Randomized Trial,” which aimed to evaluate the efficacy and safety of a knowledge translation intervention to promote the intent-to-defer approach in clinical practice [20]. The study designs have some similar components. However, they are very different. The emphasis of the Canadian research is to determine whether active knowledge translation intervention can reduce early dialysis starts. However, our study aims at evaluating the efficacy and safety of early and late dialysis initiation and the influence of timing on subsequent clinical outcomes directly.

An endpoint event-based power estimation is adopted in this study. It will allow all sites to finish together and avoid trial power being affected by alterations in accrual times. It will also protect the study power from lower than predicted event rates.

We acknowledge the following study limitations: (1) The results of the randomized study have limited generalizability due to the healthier nature of patients who participate in trials; (2) There may be a tendency for patients enrolled in clinical trials to alter their behavior due to awareness of being observed [19]. Thus, all patients may have relatively better outcomes; (3) Although this is facility-level research aimed at avoiding experimental contamination, the facilities in the routine group may also adopt the strategies in the delayed group unintentionally; (4) Patients in the routine group may actively delay their dialysis due to poor financial conditions. Thus, the eGFR rates may be similar at the end of the study and may endanger the power of this study; and (5) Patients with financial problems (e.g. without medical insurance) in both groups may get suboptimal medical care, which may impact their outcomes.

Even if the eGFR values of patients in both groups at dialysis initiation are low and not sufficiently different, this study will still potentially have economic, health, and scientific implications. Completing this study will add new knowledge about the timing of dialysis initiation.

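### The cost outcome has no common time horizon although follow-up differs by up to 30 months between patients, so unadjusted totals mix the effect of deferral with time observed

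*Protocol article*

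**What the plan says.** Three parts of the protocol article bear on this.

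- **Quantity and window (Cost measurement).** "To assess the total cost of each group, the number of resources consumed will be prospectively collected for each patient". Visit receipts record the patient's "costs during the follow-up period". No horizon is named.
- **Analysis.** "Sociodemographic, clinical, and economic data will be analyzed per group". The t-tests cover "medical expenses based on a data-paired analysis (before-after study"), with a Wilcoxon test for non-normal data. Cox analysis is named for death, cerebro-cardiovascular events and hospitalization, but not for cost.
- **Timing (Sample size and Discussion).** "The project selection window for patient enrollment is 30 months". The study ends at 198 events. Of this event-based approach the Discussion says: "It will allow all sites to finish together and avoid trial power being affected by alterations in accrual times".

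Costs appear in the quarterly columns of Table 4, before and after dialysis starts. The cost study is a secondary endpoint.

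**The concern.** With 30 months of entry and one closing date, the first patient is observed up to 30 months longer than the last. A cost summed over each patient's own follow-up therefore reflects observation time as well as strategy. Late entrants are the most likely to be cut off before or soon after dialysis starts. If deferral saves money mainly by shortening time on dialysis, part of that saving is never seen.

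The before-after comparison does not cure this. The time after dialysis start is cut by the closing date, patients not yet on dialysis have no after period, and pairing within patients is not a comparison between arms.

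Hospitals are the randomized units, eight per arm. Chance differences in when hospitals recruit can give one arm longer follow-up, and so higher recorded cost, for reasons unrelated to deferral. The Background uses the economic burden of dialysis as motivation and the Discussion expects economic implications, so a cost result that moves with recruitment dates would weaken a stated use of the trial.

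**Working it through.** **1. Reproduce the planning figures.** Inputs from Sample size: "we assume the death rate will be 30% or less within 3 years", and "a difference of 10% in death rates between these two groups is considered acceptable", read as 30% v 20%. With exponential survival the monthly hazards are −ln(0.7)/36 = 0.00991 and −ln(0.8)/36 = 0.00620, a hazard ratio of 0.626. For uniform entry over R = 30 months and closure at month T, the event probability is 1 − [exp(−λ(T−R)) − exp(−λT)]/(λR). At T = 36 this gives 0.1848 and 0.1208; times 473 these are 87.4 and 57.1 events, against the stated 87 and 57. The planning calculation thus implies closure at month 36, but the text does not state it. The operative rule is 198 events.

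**2. When would 198 events occur?**

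| Assumption | Closure (month) | Follow-up (months) |
|---|---|---|
| 473 per group, deaths only, 30% v 20% | 44.7 | 14.7-44.7 |
| 473 per group, deaths only, 30% in both arms | 39.1 | 9.1-39.1 |
| 473 per group, 30% v 20%, hazard raised 25% for nonfatal events (assumed) | about 39 | about 9-39 |
| As above, raised 50% (assumed) | about 35 | about 5-35 |
| 650 per group (473 × 198/144), deaths only, 30% v 20% | 36 (199 events) | 6-36 |

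The nonfatal rows are included because the Primary endpoint section counts such events. In every row the spread in follow-up is 30 months.

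**3. Effect on the cost contrast (illustration).** The documents give no costs, deferral times or times to dialysis. Assumed: mean time to dialysis 3-24 months (lognormal, log-SD 0.6), deferral 2-9 months, a dialysis month costing k = 3-10 pre-dialysis months, and 30% three-year mortality in both arms. Cost per patient = min(F, S) + k × max(F − S, 0), where S is the dialysis start and F the earlier of death and closure. The contrast is the routine mean minus the deferred mean. It is compared with the contrast when everyone alive is followed for 36 months.

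- Closure at month 36: ratio 0.49-0.99, median 0.75; 0.60 or less in 25% of scenarios.
- Closure at month 44.7: ratio 0.78-1.00, median 0.94. Some patients are then observed beyond 36 months, which offsets part of the loss.

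Examples with deferral 4 months, k = 6 and closure at month 36:

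| Mean time to dialysis (months) | Unadjusted | Full 36 months | Ratio |
|---|---|---|---|
| 6 | 17.04 | 18.49 | 0.92 |
| 12 | 13.18 | 17.20 | 0.77 |
| 24 | 7.33 | 13.33 | 0.55 |

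**4. Effect of recruitment dates.** If the deferred arm enters 1 month earlier or later on average, the contrast is multiplied by a median of 0.76 or 1.23 (closure at month 36), and 0.77 or 1.22 (month 44.7). At month 36 the full ranges are 0.05-0.91 and 1.09-1.93, the extremes arising mainly when deferral or k is small. A 3-month gap gives medians of 0.27 and 1.68 at month 36.

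How likely is such a gap? Assume hospitals open uniformly over 12 months, then enrol steadily to month 30 with equal weight. A hospital's mean entry is (opening + 30)/2, with SD (12/√12)/2 = 1.73 months. The difference between two means of eight has SD 1.73 × √(2/8) = 0.87. A gap above 1 month then has probability of about 25%, and above 3 months under 0.1%. With opening over 24 months the SD doubles, and the probabilities are about 55% and 8%.

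**5. Does a common horizon help?** With a 12-month horizon, closure at month 44.7, mean time to dialysis 12 months, deferral 4 and k = 6, the contrast is 9.10, 9.10 and 9.11 for the deferred arm 3 months early, level and 3 months late.

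**6. Which horizons are reachable?** Before deaths, the share with at least 24 months of potential follow-up is (36 − 24)/30 = 40% for closure at month 36, and (44.7 − 24)/30 = 69% at month 44.7. For closure at month 36, only 3/30 = 10% remain at month 33 and none at month 36.

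**The case against.** The strongest reply is that Cost measurement describes data collection, and that an article may leave the horizon and the handling of censored costs to a fuller protocol or analysis plan. That would answer mere silence. Here, however, the article names a quantity, a window and a test, and none of them deals with unequal follow-up. The reply does limit the point: the text never says that raw group sums will be the tested contrast, and quarterly records leave a sound analysis open.

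It also stands that t-tests use per-patient values. A reader might infer that the cost comparison is distorted by the number enrolled in each arm; the named tests do not support that.

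Two stronger readings are tempting. One is that the contrast is roughly halved. That is the low end of the illustration, needing late dialysis start and closure near month 36; at month 44.7 no scenario fell below 0.78. The other is that small differences in recruitment dates could erase or double it. That generally needs a gap of about 3 months across a whole arm. Even then, at closure at month 36, it occurred in only about 37% (erased) and 35% (doubled) of scenarios. No imbalance in recruitment dates is documented.

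**Conclusion.** The point holds in a limited form. As written, neither the group total nor the before-after test accounts for follow-up that differs by up to 30 months by design. That spread comes from the protocol's own timing and does not depend on any cost assumption.

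The size does depend on assumed inputs. If deferral saves cost by shortening dialysis time, unadjusted totals understate the 36-month contrast by between almost nothing and nearly half. A 1-month gap in mean entry between arms typically moves the contrast by roughly 20-30%, for closure at about month 36 to 45, and more if deferral or the cost ratio is small. These figures show sensitivity and do not predict this trial's bias. The issue concerns a secondary endpoint and leaves the primary comparison untouched.

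**What to change.** In Cost measurement and Analysis, define the cost outcome as mean cost per enrolled patient from enrolment to a common horizon that a sufficient share of patients in both arms can reach. Candidates are 24 months or the minimum follow-up at closure. Thirty-six months would not do if closure falls near month 36, because inverse-probability weights already reach 1/0.10 = 10 at month 33 and are undefined at month 36. At 24 months they would be at most 1/0.40 = 2.5 from administrative censoring.

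Keep patients who die at their actual cost. Where follow-up ends before the horizon, use the quarterly cost records with a censoring-adjusted estimator. Compare arms with confidence intervals that respect the hospital as the unit of randomization. Replace the paired before-after test for medical expenses, or state what separate question it answers.

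The change needs wording and modest programming, with no new data. The downsides are somewhat wider intervals and the exclusion of costs beyond the horizon. A very short horizon, such as 6 months, would see little of the contrast if dialysis starts late.
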